## Abstract

**Introduction:**

Over 50% of patients participating in cardiac rehabilitation (CR) experience poor sleep and/or, closely related, psychological stress. Although stress management interventions are generally available, they are typically underutilised in CR, and sleep remains an underaddressed component within CR. This is concerning, as poor sleep and stress not only reinforce each other but are also associated with poorer cardiovascular health and lower quality of life. Therefore, the primary aim of the OPtimising CArdiac REhabilitation by REfining Sleep and STress (RESST) study is to investigate the (cost-)effectiveness of adding a behavioural intervention targeted at improving sleep and managing stress during CR (RESST intervention) on sleep and psychological stress. Furthermore, the study aims to explore the (bidirectional) associations between sleep, stress and lifestyle behaviours.

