## Introduction

 Cardiac rehabilitation (CR) focuses on the secondary prevention of cardiovascular disease through a multidisciplinary approach that includes exercise training, psychosocial counselling and lifestyle education and modification.^1^ CR was shown to reduce mortality and hospital (re)admissions, and to improve quality of life (QoL) in a cost-effective manner for cardiac patients.^1^,^5^ However, despite these benefits, 10%–30% of patients experience recurrent cardiovascular events or require cardiac surgery after completing CR, indicating the need for further optimisation.^5 6^

One area with clear potential for further improvement is sleep, as this is generally unaddressed in current CR programmes. Yet, more than half of cardiac patients experience poor sleep,^7 8^ with one study reporting numbers as high as 87%.^9^ In comparison, it is estimated that around one-third of the general population experiences poor sleep.^10^,^12^ Poor sleep has been associated with lower cardiovascular health and a 50% increased risk of a recurrent cardiac event,^13 14^ as well as lower QoL, lower treatment adherence and lower self-efficacy, which may impede the effectiveness of CR.^7 15^

Similar to sleep, and highly interconnected,^16^ psychological stress is also widely present in patients with cardiovascular disease. A large meta-analysis estimated that psychological stress affects 58% of all cardiac patients.^17^ Moreover, long-term stress has been shown to predict future cardiovascular disease.^18^ Stress management programmes are often available during CR^1^ and have been shown to improve perceived stress, anxiety and depression and reduce cardiovascular event rates by 50%.^19 20^ However, stress management training during CR is often underused,^21 22^ leaving patients without the support they may need.

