The primary aim of the OPtimising CArdiac REhabilitation by REfining Sleep and STress (OPTICARE-RESST) trial is to determine the effectiveness of integrating a behavioural programme targeting sleep and stress simultaneously (RESST-intervention) into CR. We hypothesise that the intervention will not only improve sleep and stress, but also improve cardiometabolic health, lifestyle behaviours and psychosocial well-being. Moreover, we expect this intervention to be cost-effective as it may reduce (mental) healthcare uptake, hospital admissions and mortality, while improving QoL. Secondary aims are to examine the bidirectional relationships between sleep, stress and lifestyle factors to get more insight into the working mechanisms; determine whether aspects of diversity are associated with intervention effectiveness; and identify barriers and enablers of the intervention relevant to implementation in practice.

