### Patient population and randomisation

To be eligible for inclusion, participants need to (1) participate in CR at one of the study centres for any cardiac diagnosis or reason as stated in the Dutch guidelines,^1^ (2) be at least 18 years of age, (3) be proficient in the Dutch language, (4) experience poor sleep (Pittsburgh Sleep Quality Index (PSQI) >5^32^) or psychological stress (Perceived Stress Scale-10 (PSS-10) >13^33 34^) and (5) be willing to provide signed informed consent before study entry. Exclusion criteria are (1) having a severe psychiatric, cognitive or physical comorbidity that would impede CR participation and (2) active treatment for sleep disorders, stress or other forms of (behavioural) therapy at the start of the study or expected to start within 6 months that could interfere with the RESST intervention. Participants who have received prior treatment targeting sleep, stress or a related complaint (eg, continuous positive airway pressure users or sleep medication), that is still ongoing and has resulted in symptom stability in the past 3 months, are eligible.

Participants who fulfil inclusion and exclusion criteria are randomised (1:1) to the control or intervention group after baseline measurements are completed. Randomisation is performed using Castor software, which generates a random allocation sequence in variable blocks of 2, 4 and 6, stratified by participating centres. First patient inclusion took place on 28 August 2024 and is expected to last for a period of 2 years.

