#### Primary outcomes

The primary outcomes are both accelerometer-assessed and self-reported sleep, and perceived psychological stress. Sleep is objectively assessed using the GENEActiv accelerometer, which is worn on the non-dominant wrist for 7 consecutive days and nights. The GENEActiv is a tri-axial, wrist-worn accelerometer, which has shown good agreement for sleep-related parameters with gold-standard polysomnography.^38^ With validated algorithms (GGIR package in R), sleep duration, sleep latency, wake-after-sleep-onset and sleep efficiency are estimated. Sleep latency is the time it takes to fall asleep, wake-after-sleep-onset is the time spent awake between the first time falling asleep and the last time waking up, and sleep efficiency is the percentage of time spent asleep between the first time falling asleep and last awakening. Additionally, sleep quality is self-reported with the PSQI.^32^ The PSQI is a widely used tool to measure sleep quality, also in cardiac populations, and was shown to be valid in both clinical and non-clinical samples.^39 40^ Psychological stress is measured with the PSS-10, which was shown to be valid for assessing perceived stress.^41 42^

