### Statistical analysis

Descriptive statistics will be used to summarise the outcomes of the primary and secondary study parameters, as well as baseline characteristics (table 2).

Primary analyses will be conducted according to the intention-to-treat principle, but per-protocol analysis will be conducted to provide further insight into the effectiveness in adherent participants, as we aim to continue collecting data from non-adherent participants.

Linear mixed effect (LME) models will be used to study between-group differences in changes in primary and secondary endpoints between T0-T3m (primary analysis) and T0-T6m (secondary, explorative analysis). LME models can handle missing data and do not require data imputation.

To investigate whether parameters of diversity (age, sex and socioeconomic status) predict differences in changes in sleep and stress parameters between the intervention and control groups, an interaction term between randomly allocated treatment and the determinant of interest will be added to the LME model. If a significant interaction emerges, exploratory subgroup analyses may be performed.

A cost-effectiveness analysis will be performed using a healthcare and societal perspective according to the latest Dutch guidelines.^51^ A short-term time horizon of 6 months (total follow-up) will be analysed, as well as a lifetime time horizon, by using mathematical modelling for extrapolation beyond the follow-up period.^52^ Costs will include healthcare utilisation, intervention costs and productivity losses, while effects will be expressed in quality-adjusted life-years.

LMEs will also be used to examine the (bi)directional relationships between sleep, stress and lifestyle/health components. Lifestyle and health components include physical behaviour, diet intake and momentary fatigue. First, cross-sectional and longitudinal associations will be assessed using weekly averages of sleep/stress parameters and other lifestyle/health components. Additionally, day-to-day temporal relationships will be studied, while measurements on a certain moment may serve as a predictor for outcomes on a later moment. In these analyses, an outcome on a certain moment (eg, physical activity) may serve as the predictor for sleep/stress at a later moment during the day or on the following night/day, or conversely, sleep/stress at a certain moment may serve as the predictor for an outcome (eg, fatigue) during a later moment.

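### The entry rule (poor sleep or stress) selects on both variables, so baseline between-person sleep-stress associations are biased downwards; the bidirectional aim can still be addressed

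*Protocol article*

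**What the plan says.** Under Patient population and randomisation, the fourth inclusion criterion is that participants "experience poor sleep (Pittsburgh Sleep Quality Index (PSQI) >5^32^) or psychological stress (Perceived Stress Scale-10 (PSS-10) >13^33 34". The two conditions are joined by *or*, so a patient with neither complaint cannot enter.

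The same constructs are outcomes. Under Primary outcomes: "The primary outcomes are both accelerometer-assessed and self-reported sleep, and perceived psychological stress". PSQI and PSS-10 are the self-report instruments, measured at T0, T3m and T6m.

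The Introduction sets the aim: "Secondary aims are to examine the bidirectional relationships between sleep, stress and lifestyle factors to get more insight into the working mechanisms". The Statistical analysis section serves it in two steps. First, "cross-sectional and longitudinal associations will be assessed using weekly averages of sleep/stress parameters and other lifestyle/health components". Then: "Additionally, day-to-day temporal relationships will be studied, while measurements on a certain moment may serve as a predictor for outcomes on a later moment", in either direction.

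The limitations given in the strengths-and-limitations box and in the Discussion include lack of blinding, short follow-up and, in the Discussion, scarce hair samples from men. They do not mention what the entry rule does to the sleep-stress association.

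**The concern.** Every enrolled good sleeper is stressed, and every enrolled patient with low stress sleeps poorly. The group that does well on both, which would anchor a positive association, is missing. This is collider selection: conditioning on having at least one of two complaints induces a negative component in their association. Adjusting for age, sex or similar covariates does not remove it.

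The first association step compares persons within exactly this sample. A weak or absent baseline association could be a product of the inclusion criterion, yet be read as evidence against the close link between sleep and stress on which the combined intervention rests. It would also be a poor guide to mechanism, which is the declared purpose of the aim.

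**Working it through.** The article gives no figure for the association analyses, so there is none to reproduce. The check asks what the entry rule does to a known association.

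**Inputs from the article.** The rule is PSQI >5 or PSS-10 >13. For poor sleep, the Introduction says "more than half of cardiac patients experience poor sleep,^7 8^ with one study reporting numbers as high as 87" per cent. It puts stress at 58% of cardiac patients. The abstract says "Over 50% of patients participating in cardiac rehabilitation (CR) experience poor sleep and/or, closely related, psychological stress".

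**Assumptions.** The unselected correlation r (range 0.2 to 0.6; the article says only that the two are highly interconnected), bivariate normality, the 35%/35% split that makes *either complaint* about half, and a three-month stability of 0.6.

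**Step 1, hand check.** Take prevalences of 50% and 58% and r = 0.4. Simulation gives P(either) = 0.727.
- Both complaints: 0.50 + 0.58 - 0.727 = 0.353. Stress only: 0.58 - 0.353 = 0.227.
- All patients: stressed are 0.353/0.50 = 71% of poor sleepers and 0.227/0.50 = 45% of good sleepers.
- Enrolled patients: still 71% of poor sleepers, but 100% of good sleepers.

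**Step 2, continuous scores at T0.** Draw (sleep, stress) from a bivariate normal, set thresholds by prevalence, keep those above either threshold, and recompute the correlation.

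| Poor sleep / stress | r = 0.2 | 0.3 | 0.4 | 0.5 | 0.6 |
|---|---|---|---|---|---|
| 50% / 58% | -0.12 | -0.03 | 0.07 | 0.17 | 0.29 |
| 35% / 35% (either about 50%) | -0.28 | -0.20 | -0.11 | 0.00 | 0.12 |
| 87% / 58% | 0.08 | 0.18 | 0.28 | 0.38 | 0.49 |

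At r = 0.4 the loss is 0.33, 0.51 and 0.12 respectively.

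**Step 3, weekly averages.** Let each average correlate 0.6 with its questionnaire (assumption), with 50%/58% and questionnaire r = 0.4. If the averages are related only through the questionnaires, their true correlation is 0.6 × 0.6 × 0.4 = 0.144, and it falls to 0.02. If the averages themselves correlate 0.3 or 0.4, they fall to 0.19 or 0.30.

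**Step 4, follow-up (50%/58%).** The T3m sleep-stress correlation goes from 0.3 to 0.20 and from 0.5 to 0.41. The correlation of changes goes from 0.30 to 0.25 and from 0.50 to 0.45.

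For T0 stress predicting T3m sleep at r = 0.4 with no direct effect, the unadjusted slope is 0.6 × 0.4 = 0.24 in all patients and 0.04 in the enrolled. That 0.24 is confounding by T0 sleep. With T0 sleep and T0 stress both in the model, the enrolled sample returns a direct effect of 0 as 0.00 and one of 0.15 as 0.15.

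**Step 5, the other planned associations.**
- Person-centred day-to-day slope, simulated over seven days: 0.30 without selection, 0.30 with it. An uncentred pooled slope fell from 0.30 to 0.15 (between-person correlation 0.3).
- Sleep with a third variable such as physical activity, assumed r = -0.30: -0.25 to -0.29 at 50%/58%.

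**Step 6, does restriction repair the T0 slope?** Among patients with PSQI >5, everyone qualifies whatever the PSS-10, so selection depends on the predictor alone. At r = 0.4 the standardised slope of stress on sleep there is 0.40. The slope of sleep on stress among those with PSS-10 >13 is also 0.40. At 50%/58% the shares kept are 0.50/0.727 = 69% and 0.58/0.727 = 80%. At 87%/58%, where P(either) = 0.911, they are 95% and 64%.

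**The case against.** The strongest reply is that the aim does not rest on the step at issue. The next sentence of the plan sets out day-to-day lagged analyses, and the abstract assigns the bidirectional question to multilevel models of the momentary data. Selection on person-level baseline scores leaves within-person slopes intact. This stands. A reader might infer that the entry rule leaves the trial unable to answer its bidirectional aim; the article does not support that. The proviso is that within- and between-person effects are separated. The article does not say so, but that detail may fairly sit in the analysis plan.

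A reader might also infer that the association will be reversed. That depends on a correlation the article does not give: at 50%/58%, true values of 0.5 or 0.6 stay positive, and at 87% poor sleep even 0.2 does. The largest losses are for PSQI against PSS-10, whereas the quoted step concerns weekly averages, which can lose much less (step 3).

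It can further be said that the article nowhere claims its associations hold for all CR patients, and that the association among patients with a complaint is valid description of the group the intervention targets. That is fair. But a coefficient shaped by the entry rule is easily misread when the purpose is insight into mechanisms, and the Discussion presents the week-averaged view as a source of understanding without this caveat.

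Finally, the article is condensed, and a separate data analysis plan is mentioned. The point does not rest on missing detail: the entry rule and the analysis are both stated, and together they yield the bias.

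**Conclusion.** The point holds for between-person sleep-stress associations, chiefly at baseline. Under the entry rule they are biased downwards in every scenario examined: by about 0.3 at prevalences of 50% and 58%, about 0.1 if poor sleep is 87%, and about 0.5 if only half of patients have either complaint. At 50%/58%, true correlations of 0.3 to 0.6 appear as about -0.03 to 0.29. Weekly averages are attenuated to a degree that depends on how closely they track the questionnaires. Distortion is smaller for follow-up and change associations, slight for sleep or stress against lifestyle variables, and nil for person-centred day-to-day slopes.

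The direction of the bias follows from the rule. Its size rests on the assumed correlation, stability and normality. One step of a secondary, exploratory aim is affected; the randomised comparison is not. It should be corrected because the remedy is cheap and the likely error is a misleading null finding.

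**What to change.** 1. In longitudinal sleep-stress models, adjust for both T0 PSQI and T0 PSS-10, the two selection variables. All patients are kept.
2. For cross-sectional questionnaire slopes at T0, fit sleep predicting stress in patients with PSQI >5, and stress predicting sleep in patients with PSS-10 >13, at least as a sensitivity analysis. Report slopes rather than correlations, since restricting the range still lowers a correlation. The repair assumes a linear relation.
3. Report weekly-average sleep-stress associations as conditional on enrolment, make no claim about CR patients in general, and name the selection as a limitation.
4. Rest conclusions on direction on day-to-day models that separate within-person from between-person effects, for example by person-mean centring.

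Cost: analysis-plan and reporting text, using data already planned. Item 2 keeps about 65% to 95% of patients per model, depending on prevalence, so its intervals are wider. No change to eligibility, sample size or the primary analysis is needed.

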### Patient and public involvement

Patient representatives and CR professionals were involved in the initial design of the study (intervention). Additionally, a focus group interview with patients was held to evaluate the outcomes regarding completeness and relevance. The participants also provided input on the feasibility and burden of the measurements and participation in the study.

Patient meetings will be held yearly to provide input and to discuss results, where we will ensure a diverse sample of patients regarding age, sex, ethnicity, socioeconomic status and cardiac diagnosis. At the end of the study, approximately 10 interviews with patients and their relatives, and healthcare professionals will be conducted to collect information on experienced needs, barriers and enablers for further improvement and implementation of the intervention. These interviews may also guide interpretation of the differences between the intention-to-treat and per-protocol analyses, as barriers will be discussed. All interviews will be recorded, transcribed verbatim and analysed using the Consolidated Framework for Implementation Research.^53^

## Discussion

OPTICARE-RESST is a multicentre RCT aiming to include 200 CR participants experiencing poor sleep and/or psychological stress. To our knowledge, this is the first sizeable trial to evaluate a behavioural intervention simultaneously targeting sleep and stress in a cardiac population. This trial will provide insight into the (cost-)effectiveness of such a behavioural intervention on sleep and stress, the interrelatedness of sleep, stress and lifestyle factors such as physical behaviour, gather enablers and barriers for intervention implementation, and inform the optimisation of treatment for CR patients experiencing poor sleep and stress.

We expect that the newly developed RESST intervention will be effective in improving sleep and stress management as evidenced by improvements in self-reported and objective measures of sleep and stress in cardiac patients. In healthy adults, a meta-analysis demonstrated that similar interventions were effective in improving sleep quality and duration.^54^ Improvements were also seen in insomnia severity, sleep quality, fatigue, daytime sleepiness and QoL after receiving CBT-i or ACT(-i) in populations with comorbid conditions such as cardiac disease.^55^,^57^ The combined effectiveness of integrating CBT-i and ACT(-i) for improving insomnia symptoms, worry, anxiety and distress has been demonstrated in some small pilot studies in cancer- and CR patients,^58 59^ adding evidence to the suggestion that CBT and ACT may work in a complementary manner.^60^

Important strengths in the design are assessing sleep and stress both objectively and self-reported, which will provide insight into multiple facets of sleep and stress. Furthermore, the data collected with EMA gives insight into the daily lives of our participants and allows a more detailed perception of the day-to-day fluctuations that may occur, for example, in feelings of fatigue or stress, than questionnaires asking symptom recall over a previous period.^61^ By assessing in a momentary manner, recall bias is minimised. Combined with the simultaneously worn accelerometer, this allows for exploring the (bi)directional associations between eg, momentary experiences (eg, fatigue, stress or diet intake), and the 24 hours activity pattern of sleep and physical activity. As the data can be explored both cross-sectionally (averaged over a week) and momentarily across days (day-to-day), this will create more understanding of the interrelatedness of these factors. These insights, along with understanding how parameters such as age, sex and socioeconomic status affect intervention effectiveness, will help customise the intervention and promote equitable healthcare.

The study is limited by the relatively short follow-up time, which prevents evaluation of long-term effects on event recurrence or mortality. Furthermore, no blinding of participants or study personnel is possible due to the nature of the intervention. Lastly, there may be a bias in the objective measure for stress. As cortisol and cortisone are determined from the most proximal 1 cm of scalp hair, we very likely will obtain more samples from women than men, as a large number of the male CR participants might be (almost) bald.

During the project, end-users, such as patients, health practitioners and policy makers—including guideline developers and healthcare insurers—will be actively involved to develop a roadmap for further optimisation and implementation of the RESST intervention. Barriers and enablers, as well as participants’ perceptions and satisfaction, will be assessed. These barriers and enablers will inform the selection of implementation strategies, using the Expert Recommendation for Implementation Change taxonomy.^62^ This approach will maximise the real-world impact of the intervention and increase the likelihood of successful implementation if the intervention proves effective and cost-effective. If the intervention is not proven effective, the obtained insights will be essential to understand how the intervention can be improved to better meet patients’ needs.

In conclusion, we hypothesise that integrating a tailor-made behavioural intervention targeting sleep and stress into CR will significantly improve both outcomes. This is highly relevant given that over half of cardiac patients experience sleep and/or stress complaints, which negatively impact cardiovascular recovery and health, increase hospital readmissions and reduce QoL. If effective, this intervention has strong potential for implementation, offering a scalable solution to enhance patient recovery and long-term well-being.

